### 8.2.3 - Evaluation of Best Overall Response

The best overall response is the best response recorded from the start of the treatment until disease progression/recurrence (taking as reference for progressive disease the smallest measurements recorded since the treatment started). The patient's best response assignment will depend on the achievement of both measurement and confirmation criteria.

| Neuro  Status | MRI and/or CT status | | | |
| --- | --- | --- | --- | --- |
|  | CR | PR | STAB | PROG |
| Better | CR | PR | STAB | Unknown* |
| Same |  |  |  | PROG |
| Worse | Unknown* | | |  |

If objective response is unknown, than will reimage in 4 weeks and classify according to:

| Neuro  Status | MRI and/or CT status | | | |
| --- | --- | --- | --- | --- |
|  | CR | PR | STAB | PROG |
| Better | CR | PR | STAB | Unknown* |
| Same |  |  |  | PROG |
| Worse | Progression | | |  |

### 8.2.4 - Confirmation of response

Objective tumor response (Complete Response - CR or Partial Response - PR) must be confirmed by a second assessment approximately 4 weeks from the first evidence of objective tumor response. Subsequent imaging for patients with response will be performed every 6 weeks until progression of disease is determined. In the case of stable disease, follow-up measurements must have met the stable disease criteria at least once after study entry at a minimum interval of 6 weeks (see section 12.2.2).

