CT within the first 12 hours after surgery will verify catheter placement. MRI will be performed after catheter removal to assess, if possible, the volume of distribution of the infusate. While the patient is in the hospital, clinical evaluation will be performed per standard neurological-critical care guidelines. Carboplatin infusion and patient monitoring during the hospitalization will be conducted by the patient’s medical team including the neurosurgeon who performed the procedure, neuro-oncologist, nursing team and associated house staff. Thereafter, study patients will be evaluated clinically every 4 weeks for the first 16 weeks and every 8 weeks until 30 weeks. Evaluation will include full neurological and general examination, mini-mental status examination, and Karnofsky Performance Status. Serum carboplatin levels will not be assessed. MRI, performed every 2 months, will be evaluated per McDonald criteria. Additional ancillary imaging will be used when imaging changes are suggestive of a treatment related effect, or if the clinical scenario requires. Toxicity will be assessed according to the National Cancer Institute Common Terminology Criteria for Adverse Events, Version 4.0.

5.9 - Postoperative care and carboplatin infusion:

Immediate postoperative management will occur in the hospital and will follow the routine standard of the neurosurgeon and the neuro-oncology team. Vital signs and neurologic status will be assessed by nursing as per standard ICU protocol and recorded hourly for the first 24 hours after surgery and then at least every 8 hours for the remainder of hospitalization. Daily labs as per the study calendar will be assessed (see section 7). Infusion of carboplatin will occur in the hospital, primarily in the James Hospital, and will be initiated after CT confirmation of catheter location.

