Neurologic status will be monitored as per standard of care for postoperative brain tumor resection patients and is described in sections 5 and 7. Daily examinations will be conducted by the surgeon ([name], [name]) and house staff (residents). Serial vital signs and neurologic assessments by nursing staff will occur as per standard of care, including hourly assessments in the ICU during the first 24 hours after surgery and assessments every 4-8 hours thereafter. This may be adjusted based on the clinical/neurologic status of the patient. Neurologic examinations include an assessment of mental status including level of arousal and orientation, cranial nerve examination and motor/sensory examination of the extremities. Of note, the toxicities in primate studies referenced in the protocol were in a protocol for carboplatin infusion into the brain stem. We will not be performing infusion into the brain stem or any other eloquent structure as per the protocol.

5.11 - Post-discharge care / Outpatient monitoring:

Post-operative outpatient visits, laboratory tests and imaging will be in the James clinic and OSU outpatient testing facilities and will adhere to the calendar provided in the section 7.

After discharge, study patients will be evaluated clinically every 4 weeks for the first 16 weeks and every 8 weeks thereafter until 30 weeks. Evaluation will include full neurological and general examination, mini-mental status examination, and Karnofsky Performance Status. MRI, performed every 8 weeks, will be evaluated per McDonald criteria by a neuroradiologist (see below). Additional ancillary imaging will be used when imaging changes are suggestive of a treatment related effect, or if the clinical scenario requires. Toxicity will be assessed according to the National Cancer Institute Common Terminology Criteria for Adverse Events, Version 4.0

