## 6.7 - Data Saftey Monitoring Plan

The data and safety monitoring plan will involve the continuous evaluation of safety, data quality and data timeliness. Investigators will conduct continuous review of data and patient safety at their regular Disease Group meetings (at least monthly) and the discussion will be documented in the minutes. The PI of the trial will review toxicities and responses of the trial where applicable at these disease center meetings and determine if the risk/benefit ratio of the trial changes. Frequency and severity of adverse events will be reviewed by the PI and compared to what is known about the agent/device from other sources; including published literature, scientific meetings and discussions with the sponsors, to determine if the trial should be terminated before completion. Serious adverse events and responses will also be reviewed by the OSUCCC Data and Safety Monitoring Committee (DSMC). The PI will also submit a quarterly progress that will be reviewed by the committee per the DSMC plan. All reportable Serious Adverse Events (SAE) will also be reported to the IRB of record as per the policies of the IRB.

|  | Within 4 weeks prior to catheter Placement | Day of surgery, catheter placement, and infusion | Day after surgery | Post-infusion day 1 | Day 7 | Day 14 | Day 28 | Week 8 | Week 12 | Week 16 | Week 22 | Week 30 |
| --- | --- | --- | --- | --- | --- | --- | --- | --- | --- | --- | --- | --- |
| Informed Consent | X |  |  |  |  |  |  |  |  |  |  |  |
| Inclusion/Exclusion  Criteria | X |  |  |  |  |  |  |  |  |  |  |  |
| Pathology | X | X |  |  |  |  |  |  |  |  |  |  |
| Medical History | X |  |  | X |  |  | X | X | X | X | X | X |
| Concomitant Meds | X | X |  | X |  |  | X | X | X | X | X | X |
| Physical Exam and Vital Signs | X | X | X | X |  | X | X | X | X | X | X | X |
| Neurological examination | X | X | X | X |  | X | X | X | X | X | X | X |
| MMSE | X | X | X | X |  | X | X | X | X | X | X | X |
| Performance Status Determination | X | X | X | X |  | X | X | X | X | X | X | X |
| CBC with differential and platelets, | X | X | X | X | X | X | X | X | X | X |  |  |
| Comprehensive Metabolic Profile | X | X | X | X | X | X | X | X | X | X |  |  |
| Pregnancy Testing | X |  |  |  |  |  |  |  |  |  |  |  |
| MRI Brain^1^ | X |  |  |  |  |  |  | X |  | X |  | X |
| AE monitoring | X | X | X | X | X | X | X | X | X | X | X | X |
| CT Brain |  | X |  |  |  |  |  |  |  |  |  |  |

7 – Study Calendar

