## 8.2 - Secondary endpoints

Secondary endpoints include evaluations of efficacy and drug distribution. Evaluations of efficacy will include assessing the six-month progression free survival and median progression free survival, as well as the radiographic response rate. Volume of distribution of infusate will be evaluated radiographically by post-infusion MRI. Six month progression free survival is defined as the proportion of patients with stable disease at 6 months from surgery. Progression free survival is defined as time between surgery and earliest sign of disease progression or death. Overall survival is defined as the time from surgery until death.

Radiographic and Clinical Response Criteria

8.2.1 - Neurological Examination Status (compared to baseline assessment)

| Better | Must be on stable or decreasing dosage of corticosteroids |
| --- | --- |
| Stable | Failure to qualify as better or worse |
| Worse | Includes patients requiring increasing steroid dosage to remain stable |

If a patient requires a higher dose of steroid to maintain a stable neurological status, the patient will be considered worse for the purpose of response determination.

Patients who are clinically worse but whose steroids have been decreased at the time of deterioration will be considered stable until reassessed again at the baseline steroid dosage.

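### The MRI schedules in sections 5.8, 5.11, 7 and 8.2.4 conflict, and one depends on response, so progression is dated differently by outcome and six-month PFS is poorly supported

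*Protocol*

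**What the plan says.** Four places in the protocol set the MRI schedule after surgery.

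- Section 5.8: "MRI, performed every 2 months, will be evaluated per McDonald criteria".
- Section 5.11: "MRI, performed every 8 weeks, will be evaluated per McDonald criteria by a neuroradiologist". The same section says that outpatient imaging will keep to the section 7 calendar.
- Section 7, the calendar: the later visit columns are "Week 8 | Week 12 | Week 16 | Week 22 | Week 30". The MRI row is marked at baseline and at weeks 8, 16 and 30 only, and there is no visit after week 30. A footnote adds a scan after catheter removal.
- Section 8.2.4, for complete or partial responses only: the response "must be confirmed by a second assessment approximately 4 weeks from the first evidence of objective tumor response", and then "Subsequent imaging for patients with response will be performed every 6 weeks until progression of disease is determined".

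On duration, 5.11 says that "study patients will be evaluated clinically every 4 weeks for the first 16 weeks and every 8 weeks thereafter until 30 weeks". That limit is on clinical evaluation. The MRI sentences in 5.8 and 5.11 carry no end date.

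Section 8.2 defines the endpoints that depend on these scans: "Progression free survival is defined as time between surgery and earliest sign of disease progression or death", and "Six month progression free survival is defined as the proportion of patients with stable disease at 6 months from surgery". Section 9 plans descriptive statistics only.

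**The concern.** Radiographic progression can be dated no earlier than the scan that shows it. When response sets how often a patient is scanned, the endpoint is ascertained differently according to its own course, and one pooled PFS estimate mixes the two. The calendar also contains neither the confirmation scan nor the 6-weekly scans, although 5.11 says imaging keeps to it.

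The general schedule is inconsistent as well. Scanning every 8 weeks means weeks 8, 16, 24 and 32, whereas the calendar has 8, 16 and 30. Its 14-week gap spans the six-month landmark. A site following the calendar would have no scheduled scan near month six on which to judge the endpoint.

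Section 1.2 offers the efficacy results as support for later trials, so a figure that depends on which section a site followed would be carried forward.

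**Working it through.** The protocol states no figure that depends on this point, so there is none to reproduce.

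**Inputs.** Calendar scans at weeks 8, 16 and 30 (section 7); every 8 weeks (5.11; the 2 months in 5.8 is treated as the same); for responders, a confirmation scan 4 weeks after first response, then every 6 weeks (8.2.4).

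**Assumptions not in the protocol.** True progression is uniform within the window shown; detection occurs only at scheduled scans; weeks run from surgery; six months is 52/2 = 26 weeks.

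**Step 1: mean delay with regular scans (half the interval).** 6-weekly 6/2 = 3 weeks; 8-weekly 8/2 = 4 weeks; calendar gap (30 − 16)/2 = 7 weeks. Responders are dated sooner by 4 − 3 = 1 week against the 8-weekly text, and by 7 − 3 = 4 weeks against the calendar in its gap.

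**Step 2: the actual scan dates, for true progression in weeks 16 to 30.** Each sub-interval contributes its length times its mean delay, divided by 14.

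| Schedule | Next scans | Mean delay (weeks) |
| --- | --- | --- |
| Calendar | 30 | 14×7/14 = 7.0 |
| 8-weekly | 24, 32 | (8×4 + 6×5)/14 = 4.4 |
| Response first seen at week 8 | 18, 24, 30 | (2×1 + 6×3 + 6×3)/14 = 2.7 |
| Response first seen at week 16 | 20, 26, 32 | (4×2 + 6×3 + 4×4)/14 = 3.0 |
| Same, week-30 calendar scan kept | 20, 26, 30 | (4×2 + 6×3 + 4×2)/14 = 2.4 |

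**Step 3: an exception.** If the 6-weekly scans replace the calendar after a week-8 response, the scans fall at weeks 12 and 18. Progression in weeks 12 to 16 is then dated at week 18, a mean delay of 18 − 14 = 4 weeks. On the calendar or the 8-weekly schedule it is dated at week 16, a mean delay of 16 − 14 = 2 weeks. In that window responders are dated later.

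**Step 4: the six-month landmark.** Share of true progressions in weeks 16 to 26 that are dated after week 26:

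- Calendar: all wait for week 30, so 10/10 = 100%.
- 8-weekly: only those after the week-24 scan, so 2/10 = 20%.
- Responders: 20% if first response is at week 8 (scans 18, 24, 30); 0% if at week 16 (scans 20, 26).

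To show the size, assume exponential PFS, S(t) = 2^(−t/m), with every event found at a scheduled scan. The median m = 13 weeks is roughly the 3 months that section 2.3 gives for intravenous carboplatin; 17 and 26 are illustrative.

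| m | True S(26) | Calendar reads S(16) | 8-weekly reads S(24) |
| --- | --- | --- | --- |
| 13 | 25% | 43% | 28% |
| 17 | 35% | 52% | 38% |
| 26 | 50% | 65% | 53% |

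If the week-30 scan were instead taken as the six-month assessment, the calendar would read S(30) = 20%, 29% and 45%, which is too low. The calendar alone does not settle which applies.

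**Step 5: after week 30.** The calendar schedules no scan. Section 8.2.4 keeps responders on 6-weekly scans, and the MRI sentences in 5.8 and 5.11 leave the matter open for everyone else.

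**The case against.** The strongest reply is that little turns on this. The trial is a single-arm phase I study with a toxicity endpoint, efficacy is descriptive, and no comparison by response is planned. Against the 8-weekly text the responder difference averages about 1 week, and closer scanning dates progression nearer its true time, so it cannot inflate PFS. Most of the six-month effect comes from the calendar gap rather than from the responder rule. All of this stands, and it limits the weight of the point. It does not reconcile the sections, and a descriptive estimate is still distorted when detection differs within the sample.

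Some stronger readings are tempting but are not supported:

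- That PFS after week 30 rests on responders alone. Deaths in all patients are PFS events with no time limit, ancillary imaging is open to any patient, and the MRI sentences in 5.8 and 5.11 have no end date. What holds is narrower: under the calendar reading, radiographic progression after week 30 is scheduled to be looked for only in responders.
- That a response first seen at week 30 cannot be confirmed, so the response rate is understated. Section 8.2.4 itself requires the confirmation; the calendar merely has no visit for it.
- That a delay of 1 to 4 weeks can be expressed as a share of a 13-week median PFS. The first responder-only scan is at week 12 and the first 6-weekly one at week 18, so these differences arise almost entirely after that median. The number of responders is also not given, so the effect on pooled PFS cannot be computed.

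**Conclusion.** The point holds in limited form. Sections 5.8, 5.11, 7 and 8.2.4 set MRI schedules that cannot all be followed, and one is triggered by the outcome. On average, responders are dated about 1 week sooner than under the 8-weekly text and about 4 weeks sooner than under the calendar between weeks 16 and 30, with the reverse possible in weeks 12 to 16.

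The more serious consequence is for six-month PFS, where a patient followed on the calendar has no scheduled scan between weeks 16 and 30. The 100% figure is an upper bound. It assumes detection only at scheduled scans, whereas the week-22 clinical visit or an ancillary scan could reveal some of these progressions, and deaths are dated when they occur.

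Because the endpoints are secondary and descriptive, this should be corrected but does not threaten the primary objective.

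**What to change.** Reconcile sections 5.8, 5.11, 7 and 8.2.4 to one MRI schedule, counted from surgery, for every treated patient regardless of response. The 8-weekly interval already in 5.11 is one example; it places a scan at week 24, shortly before six months. Then:

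- State one common end of imaging follow-up, at which PFS without an event is censored, and amend the section 7 calendar to match. Say in 8.2 how deaths after that date are handled for PFS; they count for overall survival in any case.
- Keep the 4-week scan for confirming response, and say in 8.2.4 that it also applies to a response first seen at the last scheduled scan.
- State how progression seen on a confirmation or unscheduled scan is dated, consistently with the definition in 8.2, which takes the first sign of progression.

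The cost is protocol wording. Against the calendar, an 8-weekly schedule carried to week 32 means four scans per patient instead of three; against 5.11 it adds none. If the 6-weekly scans are dropped, scheduled detection in a responder comes about 1 week later on average and up to about 6 weeks later in the worst alignment: progression at week 16.5 would be seen at week 24 instead of week 18. Ancillary imaging under 5.11 remains available. With a common schedule, the difference in dating delay by response on scheduled scans is zero.

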# 9 - Statistical Considerations

A standard phase I study design utilizing dose escalation as defined in section 2.0 will be used. A maximum of 42 patients will be accrued. Descriptive statistics of response/efficacy and tolerance of treatments will be used. Only patients who received study drug will be considered for endpoint analysis. Patients that did not receive study treatment (catheter placement and convection enhance delivery of carboplatin) will be replaced at the current dose cohort.

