# 5 - Treatment Plan

5.1 - Study Design:

Phase I dose escalation study

5.2 - Proposed trial:

Carboplatin in a volume of 54 ml will be administered intracerebrally by convection enhanced delivery at a flow rate of 0.75 ml/hr over 72 hr. The first patient will receive an initial starting dose of 2 µg over 72 hrs (0.667 µg/24 hr). This first patient will be observed for 28 days after completion of the infusion, prior to enrollment of additional patients. In the absence of dose-limiting toxicity (DLT), 3 more patients will be entered at the next higher dose level, which will be double the prior dose (i.e., 4 µg over 72 hrs). If 1of 3 patients exhibits DLT, an additional 3 patients will be entered at that dose level. Dose escalation will continue until DLT occurs in at least 2 out of 6 patients. The maximum tolerated does (MTD) will be defined as the highest dose level at which 3/3 or 5/6 patients could be treated without DLT. Dosage escalation will proceed in subsequent cohorts of 8 µg, 16 µg, 32 µg, 64 µg, 85 µg, 107 µg and 128 µg. If the MTD has not been reached, we will submit a request to the FDA with a schedule for continued escalation until DLT is reached. If 2 of 3 patients demonstrate DLT at 2 µg, the dose will be reduced to 1 µg for the next three patients. DLTs are defined, in the presence of supportive care, as any Grade 3 or 4 toxicity that is possibly, probably, or definitely related to the study drug. The maximum tolerated dosage is defined as the dose level below that causing DLT in at least two patients. The length of the DLT window will be at least 28 days, and this time interval must elapse before completion of one cohort and initiation of the next.

5.3 - Population:

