A CT will be obtained a maximum of 12 hours before the start of the infusion to confirm catheter position. Infusions will start preferably on postoperative day 1, but could be delayed up to postoperative day 7, based on patient’s condition. If the patient’s condition does not allow for infusion, the catheters will be removed. Once catheter placement has been confirmed, patients will undergo infusion of carboplatin. Carboplatin will be infused at a rate of 0.75 mL per hour over 72 hours via a syringe pump. The total flow rate (0.75 ml/hr will be divided among the catheters placed. The catheters and syringe pumps will be attached to a bedside programmable syringe-type microinfusion pump (Medex/Medfusion 3500 Syringe pump or equivalent, which are immediately available for use) via infusion tubing (Vygon Neuro Infusor Infusion catheter system).

The infusion pump will be monitored by the surgical team, including attending neurosurgeons, resident house staff and nurse practitioners. Decisions regarding initiation of infusion and determining if there are problems with the infusion will be the responsibility of the surgical team and supervised by one of the neurosurgical attending physicians ([name]). The infusate will be prepared and supplied by The OSUMC / James Pharmacy Investigational Drug Service (see section 3) at the dose as determined by the dosing schedule (see page 18, section entitled ‘dosing paradigm’) and will be changed every 24 hours by the surgical team. A syringe-type microinfusion pump (see paragraph above) will control the rate of carboplatin infusion into the infusion catheter. The syringe will connect to the infusion catheters via infusion tubing. The infusion rate will be 0.75 ml/hr. Nursing staff will record that the infusion is running, but will otherwise have no responsibilities regarding the infusion pump. For any problems with the infusion or if the infusion pump alarms, the nurses will notify the neurosurgical team. During infusion, vital signs and neurologic status will be assessed and recorded at least every 4 hours. A specific person designated for monitoring the infusion pump and this person’s contact information will be clearly identified in the chart and provided to the patient’s nurse. This person will be a member of the neurosurgical team and will be [name], [name] or [name] or a physician or nurse directly supervised by [name], [name] or [name].

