## 5.14 - Criteria for discontinuation of treatment

- DLT as defined by grade 3 or 4 toxicity according to the National Cancer Institute Common Terminology Criteria for Adverse Events, version 4.0.
- Grade 2 intracranial hemorrhage
- Request by the patient for discontinuation.

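### Section 9 sets no minimum infusion for DLT evaluability, so a patient stopped early without a DLT can count as tolerating the full dose level

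*Protocol*

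**What the plan says.** **Planned exposure.** Section 5.2: "Carboplatin in a volume of 54 ml will be administered intracerebrally by convection enhanced delivery at a flow rate of 0.75 ml/hr over 72 hr". Dose levels in section 5.12.1 are total amounts for the whole infusion, from 2 µg (Level 1) to 128 µg (Level 9), with a Level 0 of 1 µg.

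**Who counts.** Section 9: "Only patients who received study drug will be considered for endpoint analysis".

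**Who is replaced.** Section 9: "Patients that did not receive study treatment (catheter placement and convection enhance delivery of carboplatin) will be replaced at the current dose cohort".

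**How patients are scored.** The decision table in section 5.13 classifies patients only by whether they had a DLT at a given level. It has no category for an incomplete infusion. Section 5.2 bases the MTD on 3/3 or 5/6 patients treated without DLT; section 5.12 requires at least 5/6.

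**Early stopping is foreseen.** Section 5.14 lists, besides toxicity, "Request by the patient for discontinuation". Section 5.9 says that "determining if there are problems with the infusion will be the responsibility of the surgical team". It also covers the patient who cannot start, whose catheters are removed. Neither section says how a patient who starts but does not finish is counted.

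**The concern.** The MTD is part of the primary endpoint and rests on three to six patients per level. Each DLT-free patient is taken as evidence that the level was tolerated, and that inference needs the level to have been given. A patient who received a third of the volume and then passed 28 days without a DLT says little about the full dose. Under section 9 that patient has received study drug, so is included and not replaced.

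The escalation decision is made cohort by cohort. If a level is cleared on incomplete infusions, the next cohort is exposed to a higher dose, and a later analysis cannot undo that. The MTD is also intended for use in future studies (section 1.1). The protocol's own background (section 2.5) describes primate neurotoxicity as dose-dependent and as appearing once accumulated drug reached certain amounts. It is therefore reasonable to expect lower risk after a partial infusion.

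**Working it through.** **1. The plan's own figures.** Volume: 0.75 mL/h × 72 h = 54 mL. Top concentration: 128 µg / 54 mL = 2.37 µg/mL. Both agree with the protocol (sections 5.2 and 5.12.2), so dose received = nominal dose × hours / 72.

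**2. Dose after an early stop at Level 9.**
- 24 h: 128 × 24/72 = 42.7 µg, below the full Level 6 dose (64 µg).
- 48 h: 128 × 48/72 = 85.3 µg, about the full Level 7 dose (85 µg).

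**3. When a stop delivers no more than the level below.** Hours = 72 × (lower dose / nominal dose).
- Levels 2 to 6, where the dose doubles: 72 × 1/2 = 36 h.
- Level 7: 72 × 64/85 = 54.2 h.
- Level 8: 72 × 85/107 = 57.2 h.
- Level 9: 72 × 107/128 = 60.2 h.

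At Level 9, losing about the last 12 hours means that the patient was not exposed beyond the level below.

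**4. Chance that a level is cleared.** Section 5.13 escalates on 0/3, or on 1/3 followed by 0/3. With DLT probability p per patient:

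P(clear) = (1−p)³ + 3p(1−p)² × (1−p)³

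The protocol gives no DLT rates and no early-stop rate, so the following are assumptions: the true full-dose rate is 0.33, a share s of patients stops early for a reason other than toxicity, and their DLT risk is r times the full-dose risk. Then p = 0.33 × [(1−s) + s·r].

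With all infusions complete: 0.67³ + 3(0.33)(0.67²)(0.67³) = 0.301 + 0.134 = 0.434.

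| Share stopped early | Half risk (r = 0.5) | No risk (r = 0) |
| --- | --- | --- |
| 0% | 0.434 | 0.434 |
| 10% | 0.467 | 0.500 |
| 20% | 0.500 | 0.570 |
| 30% | 0.535 | 0.641 |

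**5. Worst case, given that it has happened.** With one zero-risk patient among the first three, P(clear) = (1−p)² + 2p(1−p)(1−p)³. At p = 0.33 this is 0.449 + 0.133 = 0.582, against 0.434. At p = 0.4 it is 0.464, against 0.309.

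**6. Effect on the six-patient reading at the MTD.** Section 5.13 requires at least six patients there. For at most 1 DLT in 6 at p = 0.4:
- six full infusions: 0.6⁶ + 6(0.4)(0.6⁵) = 0.047 + 0.187 = 0.233;
- one zero-risk patient among the six: 0.6⁵ + 5(0.4)(0.6⁴) = 0.078 + 0.259 = 0.337.

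**7. Whole design.** A simulation of 20,000 trials per setting used three patients per cohort from Level 1, six required at the MTD, assumed DLT rates for Levels 1 to 9 of 0.01, 0.02, 0.04, 0.08, 0.15, 0.25, 0.33, 0.42 and 0.50, and no risk after a partial infusion. The MTD fell at Level 8 or 9 in 4% of trials with complete infusions, and in 8%, 12% and 20% when 10%, 20% and 30% stopped early. Replacing only the incomplete, DLT-free patients at a 20% stop rate brought this back to 4%.

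**The case against.** **The text does not say that any drug, however little, is enough.** A reader might infer that section 9 expressly scores a barely infused patient as a full observation. It does not. It speaks of receiving study drug and is silent on partial infusions. Because study treatment is described there as including delivery of carboplatin, and section 5.2 describes delivery as 54 mL over 72 h, one could argue that a patient stopped after a few hours did not receive it and should be replaced. This stands as far as it goes: the defect is an omission, not a stated scoring rule. It does not close the gap, because two teams could count the same patient differently and nothing in the protocol settles it.

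**Not every early stop biases the MTD upward.** A reader might infer that the error always favours clearing a dose. A stop for a DLT is counted as a DLT. Only stops without a counted DLT push upward.

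**The routes are few.** Grade 3/4 toxicity is a doubtful example, since section 5.14 itself labels that stop a DLT. An infusion problem matters only if it is not corrected and dose is lost; a corrected pump alarm need not shorten delivery. Patient request is the one clear non-DLT stop listed in section 5.14. This also stands.

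**The size is assumed.** The worst-case figures in step 5 are conditional on the event having happened and on zero risk afterwards. Section 8.1 counts toxicity attributable to the protocol and grade 2 intracranial hemorrhage as DLTs, and catheter risk does not vanish when infusion stops. Those figures are not an expected bias.

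**Conclusion.** The concern holds as an omission. Section 9 fixes the analysis population and the replacement rule without a minimum infusion, and no other section supplies one. Applied as written, a patient whose infusion ends early without a counted DLT would count as tolerating the nominal dose, which can bias escalation and the MTD upward.

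The direction rests on DLT risk rising with dose received. The size cannot be taken from the protocol: it is zero if all DLT-free patients finish. Under the assumptions in the working, at a true rate of 0.33, the rise is modest with few stops and some remaining risk (0.434 to 0.467 at 10% and half risk) and substantial with many stops and no remaining risk (to 0.641 at 30%).

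How some stops are scored also depends on an inconsistency. Sections 5.2 and 5.13 require at least a possible relation to the drug. Section 5.14 names grade 3 or 4 toxicity without attribution and lists grade 2 intracranial hemorrhage as a separate reason. Section 8.1 accepts attribution to drug or protocol and makes that hemorrhage a DLT, which 5.2 and 5.13 do not.

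**What to change.** In section 9, define the DLT-evaluable patient for escalation and MTD decisions as one who either

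- had a DLT at any time after the infusion began, or
- received at least a pre-stated share of the planned 54 mL and completed the 28-day window without a DLT.

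The sponsor sets the share. Replace DLT-free patients below it at the same level. Always keep patients with a DLT: dropping every incomplete infusion would remove DLTs and itself bias the MTD upward. Report everyone who received any drug in the toxicity listings, with actual volume and dose.

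Reconcile sections 5.2/5.13, 5.14 and 8.1 on attribution and on grade 2 intracranial hemorrhage, so that each stop has one score.

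**Cost.** The wording change is short, and volume can be recorded from the pump and the 24-hour syringe changes. The real cost is an occasional replacement: another patient having surgery and a further 28-day window. If 10% of patients fell short without a DLT, that is 0.1/0.9 = 0.11 extra patients per evaluable patient, or about one for every nine. Section 9 states that "A maximum of 42 patients will be accrued"; taken literally, replacements count towards that cap, and the text should say so.
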